#### 2.6.2. One-Year Follow-Up

At the one-year follow-up, we will carry out a reexamination similar to the one at baseline excluding blood analyses, cIMT, and VO_2max_. In addition, we will measure HRV in a subgroup of 15 rotating shift workers and 15 former shift workers presently engaged in day work, during a cross-shift period of five weeks after one year of follow-up. This is a noninvasive procedure that takes approximately 20 min. We will use high definition ECG and beat-to-beat blood pressure measurements and the validated software in the Task Force Monitor^®^ (CNSystems, Graz, Austria). This will give indices of sympathetic and parasympatetic activity by the high frequency, low frequency, and very low frequency oscillations. We will also assess time domain-derived parameters [33]. Sleep will be measured subjectively by electronically-administered questionnaires [34] sent to the participants every evening at 21:00 during the five-week period. Objective measures of sleep will be actigraphy and radar monitoring. Each participant will wear an Axivity AX3 accelerometer (Axivity Ltd., Newcastle, UK) for two weeks, which, in addition to sleep, will measure the physical activity level for that period. For five weeks, each participant will also have a bedside XeThru x4m200 radar module capable of recording body movements and respiration rate during sleep [35]. A user button on the bedside module will let the participants input exact bedtime and risetime. Parameters of sleep including total sleep time, wake after sleep onset, sleep onset latency, number of awakenings, and sleep efficiency will be inferred from the recorded signals and the user inputs, and will be used to assess overall sleep patterns during the entire shift-period of five weeks.

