### 2.8. Statistical Analyses

The statistical analyses will address the four research objectives stated earlier.

To elucidate the first objective, we will study the effect of shift-work on CVD-risk outcomes during a three-year follow-up using measurements at baseline and at the one- and three-year follow-ups. The primary comparison will be between the three-year follow-up and baseline. The exposure variable will be dichotomous with categories “shift-worker” and “day-worker” (reference category).

For the second research objective, we plan to use objectively measured sleep and subjectively measured sleep quality during the five-week shift period as continuous exposures variables and investigate associations to CVD risk factors. We will also include an analysis where sleep is considered a mediator between shift-work and CVD outcomes.

The third research objective concerns the effect of a three-month scheduled plant shutdown on CVD-risk outcomes. Measurements will be done before and after the shutdown, and we aim to investigate possible changes in this period.

The fourth research objective studies the effect of an eight-week HIIT intervention. We will look at the change in CVD-risk outcomes for the intervention group, and also compare this to the corresponding change for the control group. In addition to this intention to treat type analysis, we plan also to do a per-protocol analysis, where only persons having attended at least 40 percent of the training sessions will be counted as part of an HIIT group. The remaining persons will be considered to be part of the control group. We will also measure their degree of physical activity during the eight-week follow-up using the PAI index, and we will investigate whether this measure is associated with changes in the CVD-risk outcomes.

All the research questions involve longitudinal data with two or more time points. Linear and logistic mixed models will be used for all research questions. For the continuous outcomes, a linear mixed model will be used to analyze the data with a random intercept for worker, and adjustment for age, gender, and smoking. For the dichotomous outcomes, a logistic mixed model will be used with the same random-effect and fixed-effect variables. To control for multiple testing, we will use *q*-values, which is the false discovery rate equivalent for *p*-values [36].

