#### 2.8.2. Study Power

Based on the assumption of 60% participation, we expect approximately 125 participants at baseline. Furthermore, our power calculation assumes a dropout of 10% after one year, and 20% after three years.

We consider the first research question as the primary one, and to evaluate statistical power, we focused on the effect of shift work on change in systolic blood pressure from baseline to last follow-up. We fixed the between-subject and within-subject variability to values estimated in a similar longitudinal study [37], i.e., we assumed a between-worker standard deviation of 9.3 and a within-worker standard deviation of 7.8. Furthermore, we assumed an effect size corresponding to a yearly increase of 1.5–2 units in blood pressure in the shift group compared with the reference group of day workers. Based on these assumptions, we obtained a power of 0.56–0.80 of getting a significant effect of shift work on change in systolic blood pressure. However, to better account for the fact that we have multiple outcomes, we took this power analysis one step further. We assumed that of the variables included in our study, 1/3 had an effect size of the same magnitude as for the systolic blood pressure, while for the other 2/3 of the outcomes, we assumed there were no effects of shift-work exposure. We adjusted the *p*-values for multiple-testing using a Bonferroni correction and obtained a power of 0.57–0.95 of getting at least one significant finding when adjusted for multiple testing.

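### For outcomes measured at 0, 1 and 3 years, a random intercept alone makes the standard error of the primary three-year contrast somewhat too small if workers change at different rates

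*Protocol article*

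**What the plan says.** Section 2.8 sets one model for all continuous outcomes: "a linear mixed model will be used to analyze the data with a random intercept for worker", adjusted for age, gender and smoking. The logistic models take the same random effect. The section mentions no random slope, other within-worker covariance or robust standard error.

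Objective 1 is analysed "using measurements at baseline and at the one- and three-year follow-ups", and "The primary comparison will be between the three-year follow-up and baseline". Section 2.6.2 describes the one-year examination as "similar to the one at baseline excluding blood analyses, cIMT, and VO_2max". Blood pressure, resting heart rate, central pressure and arterial stiffness therefore have three visits. Blood markers, cIMT and VO2max have two in this analysis.

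The power calculation in section 2.8.2 has the same structure. It assumes "a between-worker standard deviation of 9.3 and a within-worker standard deviation of 7.8" for systolic pressure and gives no standard deviation for rates of change.

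**The concern.** A random intercept with independent residuals imposes one correlation on every pair of visits. The model then treats the change over three years as no more variable than the change over one year, and estimates a single residual variance from all intervals together. If workers drift at different rates, the three-year change is the most variable of the three, and the pooled variance falls short of it. The primary comparison uses exactly that interval.

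The protocol gives reasons to expect unequal rates. Plant A volunteers receive the training programme, with motivators continuing afterwards (section 2.5). Plant B has nine months of 12-hour shifts (section 2.1) and then a three-month shutdown (section 2.6.3). Workers may take extra shifts or swap them (section 2.1). The limitations section expects earlier shift work to affect later change. The adjustment set in section 2.8 contains none of these.

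At stake are confidence intervals that are slightly too narrow and p-values that are slightly too small. These p-values feed the q-values, and the affected outcomes include systolic pressure, on which the power calculation rests.

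**Working it through.** **Inputs from the protocol (section 2.8.2 unless noted).** Between-worker SD 9.3 and within-worker SD s = 7.8. Sample: "we expect approximately 125 participants at baseline". Losses: "a dropout of 10% after one year, and 20% after three years". Effect: "a yearly increase of 1.5–2 units in blood pressure in the shift group", so 3 × 1.5 = 4.5 to 3 × 2 = 6 units over three years. Visits at 0, 1 and 3 years (section 2.8).

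**Assumptions.** Two-sided alpha of 0.05, since none is stated. A 1:1 split, because sections 2.5 and 2.1 give 51 + 55 = 106 eligible shift workers among 213 employees. The SD of workers' rates of change, tau, is not given, so a range is shown. The slope is taken as independent of the intercept.

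**Step 1: reproduce the stated power.** With tau = 0, categorical visit and the stated dropout, the standard error of the three-year contrast is 2.147.
- Power at 4.5 units: Φ(4.5/2.147 − 1.96) = Φ(0.136) = 0.554.
- Power at 6 units: Φ(6/2.147 − 1.96) = Φ(0.835) = 0.798.

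The protocol states 0.56 to 0.80. Linear time gives 0.562 to 0.806. The power calculation therefore matches the random-intercept structure.

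**Step 2: what the model assumes.** The implied correlation for every visit pair is 9.3²/(9.3² + 7.8²) = 86.49/147.33 = 0.587. With tau = 2 the true correlations would be 0.58 (0–1 years), 0.53 (0–3) and 0.59 (1–3).

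**Step 3: closed form with complete data.** The variance of a worker's change over d years is 2s² + d²·tau². The three intervals have d = 1, 2 and 3, and the random-intercept fit pools them:
- model: 2s² + (1 + 4 + 9)/3 · tau² = 2s² + 4.67·tau²
- truth for the 0–3 change: 2s² + 9·tau²

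With 2s² = 121.68, the ratio of model to true standard error is:
- tau = 1: √(126.35/130.68) = 0.983
- tau = 2: √(140.35/157.68) = 0.943
- tau = 3: √(163.68/202.68) = 0.899

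The ratio is below 1 for every tau above 0. It contains neither the sample size nor the split.

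**Step 4: with the stated dropout.** The model-based standard error is compared with the true (sandwich) standard error for categorical visit and N = 125. Type I error is 2·[1 − Φ(1.96 × ratio)].

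| tau (mmHg/year) | model SE | true SE | ratio | type I error |
|---|---|---|---|---|
| 0 | 2.147 | 2.147 | 1.000 | 5.0% |
| 1 | 2.184 | 2.227 | 0.981 | 5.5% |
| 1.5 | 2.231 | 2.323 | 0.960 | 6.0% |
| 2 | 2.294 | 2.452 | 0.936 | 6.7% |
| 3 | 2.466 | 2.788 | 0.885 | 8.3% |

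Linear time gives nearly the same ratios: 0.980, 0.933 and 0.880 at tau = 1, 2 and 3. A simulation of 600 trials at tau = 2 gave a ratio of 0.942 and a type I error of 6.7%.

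**Step 5: outcomes with visits at 0 and 3 years only.** There is only one interval to estimate from. The ratio is 1.000 with complete data, and 0.997, 0.988 and 0.977 at tau = 1, 2 and 3 with 20% dropout.

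**The case against.** **The size rests on a figure the protocol does not give.** This stands. Slope SD 3 is extreme: about 95% of workers' true trends would span roughly ±18 mmHg over three years (2 × 3 × 3), and the population SD would grow from √147.33 = 12.1 to √(147.33 + 81) = 15.1. A reader might take its 8.3% error and 12% shortfall as the expected distortion, but the protocol does not support that. At slope SD 1, individual trends already spread by ±2 mmHg per year, as large as the assumed group effect, and the type I error is only 5.5%.

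**Most outcomes are not touched.** This also stands. A reader might infer that every three-year contrast is affected. Lipids, HbA1c, CRP, cytokines, cIMT and VO2max skip the one-year visit and are nearly immune.

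**The gain is small and not wholly free.** This stands in part. In 4,000 simulated trials using a normal reference distribution, type I error under the random intercept versus the unstructured covariance was 5.2% versus 5.4% at slope SD 0, 5.6% versus 5.4% at 1, 6.4% versus 5.5% at 1.5, and 6.9% versus 5.6% at 2 (Monte Carlo error about 0.35 points). A clear gain starts at about 1.5. Equal precision at slope SD 0 is a large-sample result: the mean unstructured standard error was 2.139 against an empirical 2.159. That is why the fix includes a degrees-of-freedom correction.

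**A random intercept is a standard choice, and a condensed article leaves covariance details to an analysis plan.** The plan is indeed internally consistent, and its power figure reproduces. However, section 2.8 names a structure instead of leaving it open, and extends the same random effect to the logistic models. That the intercept is the only covariance feature is an inference, though a natural one.

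**Conclusion.** The concern holds for the continuous outcomes measured at 0, 1 and 3 years. If rates of change differ between workers, the direction is certain: the random-intercept standard error of the three-year contrast is too small. The size is modest. At an assumed slope SD of 1 to 2 mmHg per year for systolic pressure it is about 2% to 6% too small, with a type I error of about 5.5% to 6.7%. The figure of 8.3% belongs to an extreme slope SD of 3.

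These sizes rest on the assumed slope SD, a two-sided 5% level, the SDs of 9.3 and 7.8, and the stated dropout. Whether the distortion is material cannot be settled from the protocol.

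A reader might also infer that the stated power is wrong. The protocol does not support that: the figure is correct under its own assumptions, and no slope SD is given from which to replace it.

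This is a cheap improvement of minor to moderate priority.

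**What to change.** For continuous outcomes with visits at 0, 1 and 3 years, replace the random-intercept-only structure in section 2.8 with categorical visit, its interaction with shift or day work, an unstructured within-worker covariance and a small-sample degrees-of-freedom correction. If that model does not converge, keep the random intercept and use worker-clustered robust standard errors. Outcomes measured only at 0 and 3 years can stay as planned.

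The cost is one sentence of analysis text and no new data. Three visits need six covariance parameters instead of two, and about 125 × 0.80 = 100 workers are expected at three years, so the small-sample cost is negligible. If rates of change do differ, intervals become slightly wider. With robust standard errors the widening would be about 2% at slope SD 1 (2.227/2.184 = 1.02) and 7% at slope SD 2 (2.452/2.294 = 1.07). That is the uncertainty the present model would leave out.

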### 2.1. Setting and Study Population

We will include two Norwegian enterprises (Plant A and Plant B) which are mainly involved in the production of insulation products. All employees (*n* = 213) will be informed of the research project via information meetings carried out by the Occupational Health Service in collaboration with plant representatives, and will be given the opportunity to participate. Based on previous experience, we expect that approximately 60% of the workers will accept the invitation. Baseline and follow-up measurements will be carried out over a period of three years in order to collect relevant data from the study participants. Overall, data collection consists of a questionnaire, a work hours register, aerobic capacity testing, and medical examinations with measurements of blood pressure, arterial stiffness, cIMT, and blood sampling. Additionally, we will include measures on sleep, physical activity, and respirable dust. The study has been approved by the Regional Ethics Committee in Oslo, REC South East B (Reference number: 2018/1258).

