#### 2.4.2. Blood Collection and Plasma Preparation

We will collect glycosylated hemoglobin (HbA1c) in Ethylene diamine tetra acetic acid (EDTA) blood. Serum for the investigation of lipids (cholesterol, low-density lipoprotein (LDL), high-density lipoprotein (HDL), and C-reactive protein (CRP) will be collected on gel tubes and centrifuged at 35 × 1000 rpm for 15 min within 60 min after the blood has been drawn from a vein. The Department of Medical Biochemistry Oslo University Hospital will analyze the samples within 48 h. HbA1c EDTA blood will be analyzed with a Tosoh G7 HPLC analyzer (Tosoh Bioscience, Inc. San Francisco, CA, USA) using the “high performance liquid chromatography” separation principle. Cholesterol, LDL and HDL in serum will be analyzed by enzymatic colorimetric method in the Cobas 8000 (Cobas 8000 Modular Analyzer Roche Diagnostics). CRP will be assed in serum using the particle-enhanced immune turbidimetric method on Cobas 8000.

We will sample nonfasting blood (tubes containing K2EDTA or serum Sep Clot Activator) at the same time of the day on all three occasions for the investigation of lipids (cholesterol, LDL, HDL), HbA1c, and CRP. The serum tubes will be centrifuged at the workplace of the participants and the blood samples will be delivered to the Department of Medical Biochemistry, Oslo University Hospital, who will analyze the samples within 24 h. Cholesterol, LDL, and HDL in serum will be analyzed by an enzymatic colorimetric method in the Cobas 8000 c702. HbA1c in EDTA blood will be analyzed with a D100 TM BioRad, which uses high performance liquid chromatography as the separation principle. Furthermore, CRP in serum will be quantified by particle-enhanced immunoturbidimetric method with a Cobas 8000 (Cobas 8000 c702).

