### 2.5. Physical Activity Intervention

The PA intervention will be carried out by the local Occupational Health Service, with support from Kristiania University College, School of Health Science. The intervention group will consist of all volunteering shift workers in plant A (out of 51 eligible workers), while a control group of shift workers will be recruited from plant B (out of 55 eligible workers). Subjects in the intervention group will perform three supervised training sessions per week for eight weeks. Training sessions will be carried out on a work site in the enterprise’s own training facilities, and will be guided by a physical therapist. Based on participant’s own choice, sessions will be performed by cycle ergometer, row machine, steep hill walking, or running. Dedicated motivators will log all performed sessions during the eight-week intervention period, and will afterwards continue to motivate coworkers to undertake regular PA during the three-year follow-up. The motivators will have regular meetings with the project leaders throughout the follow-up period. The total duration of an interval session will be 17 min, including 10 min warm-up and 3 min cool-down at 60–70% maximal heart rate (HRmax) [29]. During warm-up, participants should not experience any shortness of breath, and ideally, should rate their perceived exertion to be 11–13 on a Borg scale [30]. In extension of the warm-up, the subject will carry out a single four-minute interval at 85–95% of HRmax, rating 16–19 on Borg scale. Subjects will be instructed to strive to attain the desirable HR range within the two first minutes of the four-minute effort. All subjects will be equipped with a personal heart rate measurement device that includes Personalized Activity Intelligence (PAI), in which a high level of PAI seems to prevent or postpone CVD [31,32].

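### The objective 1 model pools two plants without a plant-by-visit term, so part of any plant difference in three-year change enters the shift effect if the shift share differs by plant

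*Protocol article*

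**What the plan says.** Section 2.1 describes a two-site cohort: "We will include two Norwegian enterprises (Plant A and Plant B"). Section 2.8 defines the exposure for objective 1 without reference to plant ("The exposure variable will be dichotomous with categories" shift-worker and day-worker) and fixes the time contrast: "The primary comparison will be between the three-year follow-up and baseline". The linear mixed model for continuous outcomes is specified "with a random intercept for worker, and adjustment for age, gender, and smoking", and the logistic model uses the same terms. Plant is not among them. Strengths and Limitation adds an intention to account for seniority in shift work and for sex, and mentions dust and physical activity as factors to be controlled. It does not mention plant.

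The only head counts by plant are in 2.5, for shift workers eligible for the exercise comparison: "out of 51 eligible workers" at plant A and "out of 55 eligible workers" at plant B. The total workforce is in 2.1 ("All employees (*n* = 213) will be informed of the research project"). The number of day workers at each plant is not stated.

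**The concern.** The estimand is a difference in change. A random intercept for worker takes out whatever is constant for that worker, including the level of the plant. It does not take out a change between baseline and year 3 that is common to one plant and absent from the other. Such a change is shared between the shift and day arms only in proportion to how each arm is divided over the plants. If the division differs, the remainder goes into the shift-by-visit coefficient. It is systematic, so it does not show in the standard error, and the planned q-values do not guard against it.

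The article gives three possible sources of a plant-specific change:
- Plant B closes for three months about two years after baseline, with its workers on paid leave (2.6.3). The wording is not limited to shift workers.
- At plant A, where the exercise programme runs, motivators go on encouraging coworkers to be active throughout follow-up (2.5), again without limiting this to shift workers.
- Blood handling is partly local: "The serum tubes will be centrifuged at the workplace of the participants" (2.4.2).

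**Working it through.** **Inputs from the article**
- Eligible shift workers: 51 at A and 55 at B (2.5), so the plant A share is 51/106 = 0.48.
- 125 participants at baseline; dropout 10% at one year and 20% at three years; between-worker SD 9.3, within-worker SD 7.8; effect 1.5–2 units per year, i.e. 4.5–6 over three years; stated power 0.56–0.80 (2.8.2).

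**Assumptions**
- Two-sided alpha 0.05 and blood pressure in mmHg.
- All employees who are not among the 106 eligible shift workers are day workers (213 − 106 = 107), and participation is equal by plant and schedule.
- Plant A share among day workers, q: 20–80%, with 10% and 90% as extremes.
- Plant difference in three-year change, D: 1–3 mmHg.

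**Step 1: the plan's own power figure.** A random-intercept model with visits at 0, 1 and 3 years, the stated SDs and dropout, and equal arms gives:
- shift-by-time slope: SE 0.709 per year, power 0.562 and 0.806;
- visit as a category, year 3 minus baseline: SE 2.147, power 0.554 and 0.798.

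Both reproduce 0.56–0.80 closely, so SE 2.147 is a fair basis for what follows.

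**Step 2: bias.** Bias = (0.48 − q) × D. Type I error = Φ(−1.96 − bias/2.147) + Φ(−1.96 + bias/2.147).

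| q | 0.48 − q | bias at D = 1 | bias at D = 3 | type I error at D = 3 |
|---|---|---|---|---|
| 0.20 | +0.28 | 0.28 | 0.84 | 0.068 |
| 0.40 | +0.08 | 0.08 | 0.24 | 0.051 |
| 0.48 | 0 | 0 | 0 | 0.050 |
| 0.60 | −0.12 | −0.12 | −0.36 | 0.053 |
| 0.80 | −0.32 | −0.32 | −0.96 | 0.073 |

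The largest value, 0.96, is 0.96/6 = 16% to 0.96/4.5 = 21% of the planned effect. If all day workers were at one plant, the fraction of D that enters would reach its limits of +0.48 or −0.52.

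**Step 3: price of the extra term.** Variance inflation = 1/(1 − φ²), where φ is the correlation between shift status and plant. With 64 shift workers (0.6 × 106) and 61 day workers (125 − 64), it is 1.10 at q = 0.20, 1.00 at q = 0.48 and 1.12 at q = 0.80. The interval is at most √1.12 = 1.06 times as wide.

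Power of the slope model with plant and plant-by-time added, for 1.5 and 2 units per year:

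| q | power |
|---|---|
| 0.48 | 0.562 / 0.806 |
| 0.40 | 0.559 / 0.803 |
| 0.60 | 0.556 / 0.800 |
| 0.25 | 0.538 / 0.782 |
| 0.75 | 0.529 / 0.774 |
| 0.10 | 0.484 / 0.726 |
| 0.90 | 0.471 / 0.711 |

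The loss is under 1 point for a 40–60% split, about 2–3 points at 25% or 75%, and about 8–9 points at 10% or 90%.

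**The case against.** **The imbalance is not shown.** The bias is exactly zero if day workers divide over the plants as shift workers do, and the article does not give their division. It supports no figure for a plant difference in change either. Moreover, 51 and 55 are eligible, not enrolled, counts, so 0.48 is itself an approximation. All of this stands. It makes the point conditional but does not remove it: nothing in a non-randomised two-site cohort equalises the split.

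**The size is modest.** The worst case in the assumed range is under half a standard error (0.96/2.147 = 0.45), and for a 40–60% split the type I error hardly moves. This also stands and limits the weight of the point.

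**Measurement is largely standardised.** Routine blood samples go to one hospital laboratory and are drawn at the same time of day, plasma for cytokines is frozen with a control on each plate, and one device is named for each vascular measure. A reader might infer that operators, rooms or visit dates differ by plant at each wave. The article does not say so, and on-site centrifugation is the only local handling step relied on here.

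**The covariate list may not be closed.** The article is condensed, and an analysis plan may add terms. But the article does state a covariate list, and its later remarks on seniority, sex, dust and physical activity do not add plant. The point therefore concerns a stated choice.

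**The remedy does not reach the best-documented plant events.** The exercise programme is offered to plant A shift workers, and the intensified schedule is a change to plant B's shift plan. Both act on one plant's shift workers only, so a plant-by-visit term does not remove them. This is correct and must be said next to the remedy.

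**Conclusion.** The point holds in a conditional form. The stated model has no plant-by-visit term, so (0.48 − q) × D of any plant difference in three-year change enters the shift effect. On the assumed ranges this is 0–0.96 mmHg, at most 16–21% of the planned effect, with a type I error of 5–7%. At q of 10% or 90% and a 3 mmHg plant difference, the slope model gives a bias of 1.14–1.26 mmHg and a type I error of 8.4–9.1%. The day-worker split and the plant difference are both assumptions, and 0.48 rests on eligible rather than enrolled workers.

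Two stronger readings are tempting. One is that a plant difference in change is counted in full as a shift effect; only the share difference times the plant difference enters, at most about half here. The other is that the primary result is demonstrably biased; the article does not show that the shares differ. This is a worthwhile, inexpensive safeguard and not a fatal defect.

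**What to change.** In 2.8, add plant and plant-by-visit as fixed effects to the objective 1 models, so that the shift effect becomes the within-plant shift-minus-day difference in change, pooled over plants. A plant main effect alone would change little, because the worker intercept already absorbs differences in level. Report the two plant-specific shift-minus-day estimates beside the pooled one, and the number of shift and day workers enrolled at each plant.

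State the limit in the same place: the added term removes only trends common to shift and day workers of a plant. Effects of the exercise programme on plant A shift workers and of the intensified plan on plant B shift workers stay in the pooled estimate. The plant-specific estimates can show them but do not remove them.

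Cost: a sentence or two and three extra parameters with three visits (one for plant, two for plant-by-visit). The interval is at most about 6% wider for a 20–80% split of day workers. If the split turned out as extreme as 10% or 90%, about 8–9 points of power would be lost, but that is also where the unadjusted estimate is most exposed.
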